#### Emergency surgery

##### A) Procedure

Patients will be operated according conventional standards within 24 hours after randomization. Whether a (palliative) resection or fecal deviation is done is at the discretion of the surgeon. Surgical options according to current standards are loop colostomy (blow-hole), resection with primary anastomosis with or without ileostomy, Hartmann's procedure, (sub)total colectomy with ileostomy or ileorectal anastomosis.

##### B) Post-procedure

After emergency surgery when the condition of the patient is stabilized, tumor staging of the disease will be performed (CT-scan/plain chest X-ray). In case of a colostomy an attempt at restoration of bowel continuity should preferable be performed within 3–6 months after inclusion. The colostomy will serve as a definitive solution if the patient refuses a re-operation or when a re-operation is judged to carry an unacceptable risk (ASA IV of V).

#### Surgical re-anastomosis

Candidates for surgical re-anastomosis will be operated on after completion of tumor staging and when considered stable. If possible and convenient, patients will be discharged between diagnostic work-up and re-anastomosis.

After preoperative bowel preparation and administration of antibiotics both according to the hospital protocol a re-anastomosis will be performed in accordance with conventional standards.

### Statistical analysis

#### Intention to treat

The analysis will be performed in accordance with the intention to treat principle.

#### Sample size calculation

Including 120 patients and randomizing them on a 1:1 basis will have 80% power to detect an effect size of 0.5 on the EORTC QLQ-C30 global health scale, using a two group t-test with a 0.05 two-sided significance level [19,20].

An effect size of 0.5 is chosen because a recent systematic review based on 38 studies, indicated a "remarkable universality" among estimates of clinical significance that centered around 0.5 effect size [21]. These authors recommend an effect size of 0.5 to serve as a default value for clinically significant change on quality of life measures used with chronic disease patients, when more specific information is missing, as is the case in patients with malignant colonic obstruction. Sloan et al. argue that a 0.5 effect size is even a conservative estimate that is likely to be clinically meaningful [22]. Based on these data we expect an effect size of 0.5 to be realistic in our group of patients.

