**Methods/design:**

Patients with acute left-sided malignant colonic obstruction eligible for this study will be randomized to either emergency surgery (current standard treatment) or colonic stenting as bridge to elective surgery. Outcome measurements are effectiveness and costs of both strategies. Effectiveness will be evaluated in terms of quality of life, morbidity and mortality. Quality of life will be measured with standardized questionnaires (EORTC QLQ-C30, EORTC QLQ-CR38, EQ-5D and EQ-VAS). Morbidity is defined as every event leading to hospital admission or prolonging hospital stay. Mortality will be analyzed as total mortality as well as procedure-related mortality. The total costs of treatment will be evaluated by counting volumes and calculating unit prices. Including 120 patients on a 1:1 basis will have 80% power to detect an effect size of 0.5 on the EORTC QLQ-C30 global health scale, using a two group t-test with a 0.05 two-sided significance level. Differences in quality of life and morbidity will be analyzed using mixed-models repeated measures analysis of variance. Mortality will be compared using Kaplan-Meier curves and log-rank statistics.

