## Background

Colorectal cancer is the second most common cancer in women and the third most common in men in the Netherlands [1]. The incidence in the Netherlands in 2003 was 9898 new cases, men and women were equally affected (Dutch Cancer Registry) [2]. Literature shows that between 7 and 29% of the patients present with a sub-total or total bowel obstruction [3,4].

Conventionally these patients are treated with emergency surgery to restore luminal patency. These emergency operations, involving an unprepared and obstructed bowel, include a variety of procedures ranging from a loop colostomy (blow-hole) to a Hartmann's procedure or even a subtotal colectomy. These interventions have a mortality rate of 15–34% and a morbidity rate of 32–64% despite advances in perioperative care [4-8]. It is well recognized that in a considerable number of these patients the ostomies will not be closed because of old age, metastatic disease or poor condition [3,7]. Patients with a permanent stoma do report a significant lower health-related quality of life than comparable patients without colostomy and require costly stoma material [9-12].

Since the early 1990s colonic stenting has been introduced, mainly in the left-sided colon, to restore luminal patency. It can be applied as a preoperative treatment to prepare patients for elective surgery as well as a definitive palliative procedure in patients with incurable disease [13]. In uncontrolled studies stent placement before elective surgery has been suggested to improve the patients' clinical condition, decreasing mortality, morbidity and number of colostomies [4,5,7,8]. Additionally this temporary procedure gives the opportunity to perform accurate tumor staging, leading to avoidance of surgery in patients with disseminated disease or unacceptable surgical risk [7,14-16]. In these patients the colonic stent may serve as permanent palliation. Colonic stenting also creates the opportunity to give neo-adjuvant therapy, improving patients' prognosis.

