### Data analysis

Differences in quality of life and morbidity will be analyzed using mixed-models repeated measures analysis of variance, accounting for differences in survival between groups. Mortality will be compared using Kaplan-Meier curves and log-rank statistics.

The primary analysis of the quality of life data will be performed using mixed-models analysis of variances for repeated measures. Missing data will be handled based on available data approach.

We will apply an extension of the Q-Twist method to estimate differences in quality-adjusted survival between groups.

A data and safety monitoring committee will safeguard trial continuation based on safety and effectiveness data. They will perform an interim analysis after 60 included patients have reached a one month follow-up.

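### The stated 80% power does not follow from its own inputs: 120 patients give 77.5% for the named t-test, and the figure of 120 leaves no room for losses

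*Protocol article*

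**What the plan says.** The section on sample size calculation in the protocol article states that "Including 120 patients and randomizing them on a 1:1 basis will have 80% power to detect an effect size of 0.5". The outcome is the EORTC QLQ-C30 global health scale, and the calculation is made "using a two group t-test with a 0.05 two-sided significance level". The abstract (Methods/design) repeats it: "Including 120 patients on a 1:1 basis will have 80% power to detect an effect size of 0.5".

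Neither place mentions an allowance for death, drop-out or unreturned questionnaires. On incomplete data, the section on data analysis says only this: "Missing data will be handled based on available data approach". The same section makes a repeated-measures mixed model the primary analysis of quality of life. Under data collection and monitoring, questionnaires are due on the day of randomization and at weeks 4, 12 and 24.

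**The concern.** Every input to the power calculation is given, and the effect is standardized, so no standard deviation or other unstated figure is needed. The result can be checked directly, and it does not come out at 80%.

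A second point follows. The article foresees incomplete quality-of-life data. The Background says of emergency surgery: "These interventions have a mortality rate of 15–34" (per cent). The stenting procedure section describes patients who will count as drop-outs, and follow-up questionnaires are sent by post up to week 24. If 120 is already short when everyone is evaluable, none of this has been allowed for.

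What is at stake is how the result is read. This is the only power figure in the article, and a reader of a null quality-of-life result will take it at face value.

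**Working it through.** **Inputs** (all from the section on sample size calculation): 120 patients, 1:1, so n = 60 per arm; effect size d = 0.5; two-group t-test; two-sided alpha 0.05; stated power 80%.

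**1. The stated figure, exact t-test.**
- Degrees of freedom: 2n − 2 = 118. Critical value: 1.980.
- Noncentrality: d × √(n/2) = 0.5 × √30 = 2.739.
- Power from the noncentral t distribution: **77.5%**. The stated 80% is not reproduced.

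**2. Other readings.**
- Normal approximation: Φ(2.739 − 1.960) = Φ(0.779) = 78.2%. Closer, but not the named test and still not 80%.
- One-sided alpha 0.05: 85.9%. This contradicts the two-sided level in the text.

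**3. Number needed for 80%.**
- Normal approximation: n = 2 × (1.960 + 0.842)² / 0.5² = 62.8, so 63 per arm, 126 in total.
- Exact t-test: 63 per arm gives 79.5% and 64 per arm gives 80.1%, so 128 in total.
- The shortfall is 6 to 8 patients. Because 120 is below the number of *evaluable* patients required, it cannot include an allowance for losses. An allowance would push the number above 126 to 128.

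**4. Effect detectable with 80% power at 60 per arm:** 0.516 SD, about 3% above 0.5.

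**5. The same t-test with losses.** The documents give no loss rate for quality of life, so these rates are assumptions, applied equally to both arms.

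| Assumed loss | Evaluable per arm | Power at d = 0.5 | Effect detectable with 80% power |
|---|---|---|---|
| 0% | 60 | 77.5% | 0.52 |
| 10% | 54 | 73.1% | 0.54 |
| 20% | 48 | 67.9% | 0.58 |

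**6. The planned analysis.** The primary analysis is a mixed model over three follow-up visits. For an effect averaged over those visits, with an assumed common correlation ρ and no baseline adjustment, the variance factor is (1 + 2ρ)/3. The effective standardized effect is then 0.5 / √((1 + 2ρ)/3). Patients are taken as either complete or wholly lost.

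| Assumed ρ | Effective effect | 60 per arm | 54 per arm | 48 per arm |
|---|---|---|---|---|
| 0.5 | 0.612 | 91% | 88% | 84% |
| 0.7 | 0.559 | 86% | 82% | 77% |

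For a single follow-up visit adjusted for baseline at an assumed r = 0.5, the effective effect is 0.5 / √(1 − 0.25) = 0.577. With 48 per arm that gives 79.9%.

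**The case against.** The strongest reply is that the t-test is a planning simplification and that the trial will be analysed with a mixed model on all available data. That stands. A reader might infer from the t-test figures that the trial's real power for quality of life is well below 80%. The documents do not support this. Under the assumed correlations in the working, the planned model gives about 77% to 91% for an effect averaged over visits, even with up to 20% loss. A contrast at a single visit would gain less. The protocol gives no correlation, so neither conclusion can be read from it.

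It is also tempting to turn the Background mortality range into a loss rate. That range comes from literature on emergency surgery in general. This trial excludes ASA IV and V, peritonitis, perforation, fever and sepsis, as well as patients unable to complete questionnaires, so its mortality may be lower. A patient who dies after week 4 or week 12 can still contribute earlier scores. A trial nurse safeguards collection and telephones every two weeks, also about missing items. No mortality rate for the stent strategy as a whole is given either, so loss scenarios that differ by arm would need an unsourced figure.

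Finally, the gap before losses is small, and the protocol takes 0.5 as a general default. A detectable effect of 0.52 instead of 0.50 would change no design decision. This also stands, and it bears on the weight of the point. It does not make the stated figure right. Nor does it matter that the article condenses a fuller protocol: the statement is complete in itself, and no omitted allowance could be contained in 120.

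**Conclusion.** The power statement is wrong as written. The named test with the stated inputs has 77.5% power (78.2% by the normal approximation), and 80% needs 128 evaluable patients (126 by the normal approximation). This part rests on no assumption beyond the inputs in the text and the usual conditions of the t-test. It also follows from the numbers alone that 120 includes no allowance for deaths or missing questionnaires.

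How far the t-test figure falls depends on a loss rate that the documents do not give. The 73% and 68% are illustrations at assumed losses of 10% and 20%. The point is confined to the stated calculation and does not show that the primary mixed-model analysis is underpowered. With a shortfall of 2.5 percentage points before losses and a remedy in the text alone, it should be corrected but does not rank among the critical points.

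**What to change.** Make the same change in the sample size section and in the abstract, in one of two ways.

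- **Keep the t-test.** Suggested wording: *120 patients (60 per arm) give about 78% power for an effect size of 0.5, or 80% for 0.52, with a two-group t-test if all are evaluable.* Add that this figure falls with losses, with the 10% and 20% cases given as examples and labelled as assumptions.
- **Use the planned analysis.** Base the power statement on the repeated-measures model, and state the contrast (averaged over visits or at one visit), the loss rate, the assumed correlation and whether baseline is adjusted for. A figure of 80% may then still be attainable, as the baseline-adjusted example with 48 per arm shows.

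The second option is preferable because the power statement would then describe the analysis that will be run. A t-test figure with losses should not be presented as the power of the primary analysis.

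The cost is a change of text and, under the first option, a slightly less favourable stated figure. No extra patients are needed.

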### Data collection and monitoring

Patients will be followed for a period of 6 months. The questionnaires (EORTC QLQ-C30, EORTC QLQ-CR38, EQ-5D and EQ-VAS) are filled in by the patients on the day of randomization and on week 4, 12, and 24 after randomization. In addition the patients will be asked to hand out a small questionnaire on informal care to their caregivers on week 4, 12 and 24. The questionnaires will be sent to the patients by post, collection will be safeguarded by a trial nurse. The trial nurse will also follow the patients during their hospital stay after the intervention and contact them by telephone every two weeks to assess complications, re-interventions, re-admissions, visits to the outpatient clinic and missing items of the collected quality of life questionnaires. An electronic Case Record Form (CRF) will include general patients' data (sex, age, localization tumor, etc.), patients' responses to quality of life questionnaires (EORTC QLQ-C30, EORTC QLQ-CR38, EQ-5D and EQ-VAS), informal care questionnaires and data concerning type of intervention, complications, mortality, duration of hospital and intensive care stay. This electronical Case Record Form is based on the paper source filled out by the treating physician or the patient him-/herself and put into the data base by a trial nurse. The trial coordinator will monitor the data of every included patient.

### Data analysis

Differences in quality of life and morbidity will be analyzed using mixed-models repeated measures analysis of variance, accounting for differences in survival between groups. Mortality will be compared using Kaplan-Meier curves and log-rank statistics.

The primary analysis of the quality of life data will be performed using mixed-models analysis of variances for repeated measures. Missing data will be handled based on available data approach.

We will apply an extension of the Q-Twist method to estimate differences in quality-adjusted survival between groups.

A data and safety monitoring committee will safeguard trial continuation based on safety and effectiveness data. They will perform an interim analysis after 60 included patients have reached a one month follow-up.

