### Outcome parameters

Effectiveness and costs of both strategies will be compared. Effectiveness will be evaluated in terms of quality of life, morbidity and mortality. Quality of life will be measured with the following standardized questionnaires: EORTC QLQ-C30 (European Organization for Research and Treatment of Cancer (EORTC) Quality of Life Questionnaire C30), the colorectal cancer specific EORTC QLQ-CR38 (European Organization for Research and Treatment of Cancer (EORTC) Quality of Life Questionnaire CR38), the EQ-5D (EuroQol 5 dimensions) and the EQ-VAS (EuroQol visual analogue scale). Morbidity is defined as every event leading to hospital admission or prolonging hospital stay. Mortality will be analyzed as total mortality as well as procedure-related mortality.

Cost items will include costs of hospital admissions and readmissions (operation, nursing days, outpatient visits), institutional care (nursing homes, hospice), home care, medication and other health care providers as well as direct non-medical costs (travel expenses).

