##### D) Elective surgery after stenting

Candidates for elective surgery will be operated on after completion of the preoperative screening, preferably between day 5 and 14 after inclusion, at the latest four weeks after inclusion. If possible and convenient, patients will be discharged between diagnostic work-up and surgery. After preoperative bowel preparation and administration of antibiotics both according to the hospital protocol resection of the tumor will be performed, the extension of which will be determined by the specific characteristics of the malignant process. During surgical exploration, the position and efficacy of the stent will be evaluated.

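### Morbidity is defined and collected as hospital events but is assigned to a repeated-measures ANOVA, and its definition does not exclude admissions that the protocol itself plans

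*Protocol article*

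**What the plan says.** All references are to the Protocol article.

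- **Definition** (Outcome parameters, repeated in the abstract): "Morbidity is defined as every event leading to hospital admission or prolonging hospital stay". No scale is given (count, yes/no or rate), and planned admissions are not excluded.
- **Collection** (Data collection and monitoring): "Patients will be followed for a period of 6 months". The trial nurse follows patients in hospital and will "contact them by telephone every two weeks to assess complications, re-interventions, re-admissions". Only the questionnaires have fixed time points: randomisation and weeks 4, 12 and 24.
- **Analysis** (Data analysis, repeated in the abstract): "Differences in quality of life and morbidity will be analyzed using mixed-models repeated measures analysis of variance". In Data analysis the sentence continues "accounting for differences in survival between groups", without saying how. The rule "Missing data will be handled based on available data approach" stands in the next paragraph, which concerns quality of life.
- **Planned admissions, stent arm** (Elective surgery after stenting): "If possible and convenient, patients will be discharged between diagnostic work-up and surgery". The operation falls within four weeks of inclusion.
- **Planned admissions after a colostomy** (Emergency surgery, Post-procedure; Surgical re-anastomosis): bowel continuity is preferably restored at 3–6 months, and "If possible and convenient, patients will be discharged between diagnostic work-up and re-anastomosis".

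Morbidity is one of three components of effectiveness (Study objectives), and the hypothesis in Final analysis expects stenting to lower both morbidity and mortality.

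**The concern.** The stated definition and the stated method do not fit each other. Three consequences follow.

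1. **No repeated score exists.** Someone must cut the 6 months into periods and score each one. The estimate then depends on a choice the article does not make.
2. **Death ends the event record.** A patient who dies early contributes no later events. If frail patients die more often in one arm, the survivors there look healthier. The trial's own hypothesis predicts unequal mortality, and Background gives 15–34% mortality for emergency surgery.
3. **Planned treatment can be scored as harm.** A patient sent home and brought back for the scheduled resection or stoma closure has been admitted to hospital. Discharge in between is left to local convenience across 15 hospitals, so coding may differ by centre as well as by arm.

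At stake is the interpretability of one of the three effectiveness outcomes. The sample size rests on the EORTC QLQ-C30 global health scale and is not affected.

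**Working it through.** The article states no morbidity figure, so there is none to reproduce. The checks below size the two mechanisms. Inputs not attributed to the article are assumptions.

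**A. Early death and available periods.** Assume identical complication risks in both arms, 30% frail patients and 12 fortnights (j = 0 to 11). The event probability per fortnight is 0.5·e^(-0.2j) for frail patients and 0.08·e^(-0.2j) for others. Only frail patients die, half after the first fortnight and half after the second. If a fraction d of the frail die:

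- frail share among those alive: 0.30 at j = 0; 0.3(1 - d/2)/[0.7 + 0.3(1 - d/2)] at j = 1; 0.3(1 - d)/[0.7 + 0.3(1 - d)] from j = 2
- mean events among those alive: (0.08 + 0.42 × share)·e^(-0.2j), averaged over the 12 fortnights
- weights e^(-0.2j): 1 at j = 0, 0.8187 at j = 1, and 3.1975 in total for j = 2 to 11

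*Moderate scenario: 25% v 10% of frail patients die* (7.5% v 3% of the arm).

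- d = 0.25: shares 0.300, 0.273, 0.243; (0.206 + 0.159 + 0.582)/12 = 0.079
- d = 0.10: shares 0.300, 0.289, 0.278; (0.206 + 0.165 + 0.630)/12 = 0.083
- Ratio 0.95: the arm with more deaths looks about 5% less morbid.

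*Extreme scenario: 25% v 10% of the whole arm die, all of them frail* (0.25/0.30 = 83% v 0.10/0.30 = 33% of the frail).

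- d = 0.833: shares 0.300, 0.200, 0.067; (0.206 + 0.134 + 0.345)/12 = 0.057
- d = 0.333: shares 0.300, 0.263, 0.222; (0.206 + 0.156 + 0.554)/12 = 0.076
- Ratio 0.75: about 25%.

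Simulation under the same assumptions returned the same means. The proportion with any event or death was 52% v 52% in the moderate scenario and 53% v 53% in the extreme one.

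**B. Does a days-alive offset cure this?** Take events per fortnight lived in the extreme scenario.

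- d = 0.833: events 0.206 + 0.875 × 0.134 + 0.75 × 0.345 = 0.582; fortnights 1 + 0.875 + 10 × 0.75 = 9.375; rate 0.062
- d = 0.333: events 0.206 + 0.95 × 0.156 + 0.90 × 0.554 = 0.853; fortnights 1 + 0.95 + 10 × 0.90 = 10.95; rate 0.078
- Ratio 0.80. Most of the distortion remains, because the survivors are still a selected group.

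**C. Type I error of the ANOVA.** A Gaussian mixed model was fitted to overdispersed counts in windows of weeks 0–4, 4–12 and 12–24, with 60 patients per arm, equal event rates while alive and deaths unrelated to frailty (150 runs, Monte Carlo error about 2–3 points). The nominal level is 5%.

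| Mortality | Windows after death scored zero | Available windows only |
|---|---|---|
| 15% v 15% | 5.3% | 5.3% |
| 15% v 5% | 6.0% | 5.3% |
| 34% v 5% | 14.0% | 6.7% |

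Non-normality alone does no visible harm. How periods after death are scored can matter, and the article does not settle it.

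**D. Planned admissions.** Let p be the share of stent patients discharged and readmitted for resection, and q the share of surgery patients with a stoma closure inside 6 months, ignoring stoma closures in the stent arm. The literal definition adds p - q events per patient to the stent-minus-surgery difference. With p from 0.25 to 0.75 and q from 0.2 to 0.6, the limits are 0.25 - 0.6 = -0.35 and 0.75 - 0.2 = +0.55.

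**The case against.** **Survival is not ignored.** The analysis sentence says survival differences will be accounted for. Mortality has its own Kaplan–Meier and log-rank comparison, and an extension of Q-TWiST addresses quality-adjusted survival. The available-data rule sits with quality of life, so applying it to morbidity is an inference. An article may leave such detail to a fuller document. All of this stands. A reader might infer that the plan overlooks death, and the text does not support that. What remains is that the model it names for morbidity does not itself treat death as terminal.

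**The bias may be small.** This also stands. A reader might infer a spurious advantage of about 25% for the arm with more deaths, but that needs 83% v 33% of frail patients to die within four weeks. Nor do the calculations support a claim that non-normal data invalidate the test.

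**Morbidity naturally means complications.** On this view a scheduled operation is treatment and not a morbid event, and the case record form collects complications alongside re-admissions, so the two can be told apart. That reading is reasonable and may be what was meant. However, the printed definition turns on admission or prolonged stay and makes no exception. A reader might also infer that planned readmissions penalise the stent arm. The documents do not support that either, because stoma closures fall mainly in the other arm and the net direction is open.

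**Adding death merges two outcomes that the protocol keeps apart.** This is a fair cost. Showing the components separately limits it.

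**Conclusion.** The concern holds as a mismatch between things the article positively states: an event-based definition, continuous event collection, and a model for scores at scheduled visits. It is not merely a missing detail.

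The distortion from death is about 5% in the moderate scenario and about 25% only in the extreme one. Both rest on assumed frailty, event rates and timing of deaths. Planned admissions could shift the arm difference by -0.35 to +0.55 events per patient under assumed frequencies, with no predictable sign. The documents do not show that the morbidity result will favour either arm.

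The change should be made, but the primary quality-of-life comparison does not depend on it.

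**What to change.** 1. Remove morbidity from the ANOVA sentence in Data analysis and from the matching sentence in the abstract.
2. Define the main morbidity measure as at least one unplanned event (leading to admission or prolonging stay) or death within 6 months of randomisation. Exclude admissions that the protocol plans for resection or stoma closure, but count complications that arise during them.
3. Report a risk difference and a risk ratio with 95% CI, and show unplanned events and deaths separately.
4. Give event counts only as a supplementary analysis, by a recurrent-event method that treats death as terminal, such as the mean cumulative number of events or a joint model. A negative binomial model with a days-alive offset is not enough (working, part B).

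**Cost.** Wording and a routine change of method. The events are already collected in hospital and by the two-weekly calls, and no clinical management changes. A yes/no measure loses information on repeat events and combines morbidity with death. It is also coarse at this sample size. With 60 per arm and 50% v 25.5% (assumed), power is Φ{[0.245 - 1.96·√(2 × 0.3775 × 0.6225/60)] / √(0.5 × 0.5/60 + 0.255 × 0.745/60)} = Φ(0.0715/0.0856), about 80%. Smaller reductions should be read from the confidence interval and not from a test.

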##### C) Post-procedure

Successful decompression is defined as restoration of intestinal transit based on resolution of obstructive symptoms on plain abdominal X-ray, production of stools and/or resolution of nausea and vomiting. If successful decompression is achieved and the condition of the patient is stabilized, tumor staging of the disease will be performed (CT-scan/plain chest X-ray) within one week. If any of the following conditions will be present, patients will be considered not suitable for surgical therapy and the self-expandable stent will serve as a palliative therapy: patients at high risk due to persistent comorbidity, advanced pelvic disease, peritoneal carcinomatosis and/or unresectable metastatic lesions. If decompression is not achieved within time frame of 3 days, or if clinically required, patients will be treated surgically but will not cross over to the surgical arm in the analysis.

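### Kaplan-Meier is the only method named for mortality; for procedure-related death its curves overstate the risk slightly, while the log-rank test and total mortality are unaffected

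*Protocol article*

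**What the plan says.** Under Outcome parameters, the protocol article makes mortality two outcomes: "Mortality will be analyzed as total mortality as well as procedure-related mortality". Under Data analysis it gives a single method: "Mortality will be compared using Kaplan-Meier curves and log-rank statistics". That sentence is not limited to total mortality, and the article nowhere mentions competing risks, cumulative incidence or the handling of deaths from other causes.

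Four further statements bear on whether this matters:

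- Follow-up (Data collection and monitoring): "Patients will be followed for a period of 6 months".
- Early procedures. For emergency surgery: "Patients will be operated according conventional standards within 24 hours after randomization". For elective surgery after stenting: "preferably between day 5 and 14 after inclusion, at the latest four weeks after inclusion".
- A late procedure inside follow-up (Emergency surgery, Post-procedure), for patients with a colostomy: "restoration of bowel continuity should preferable be performed within 3–6 months after inclusion".
- Incurable disease (Colonic stenting, Post-procedure). Among the conditions that make the stent a palliative treatment are "advanced pelvic disease, peritoneal carcinomatosis and/or unresectable metastatic lesions". These patients stay in the trial and are analysed by intention to treat.

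**The concern.** Procedure-related death is a cause-specific event. A patient who dies of cancer or comorbidity can no longer die from a procedure, yet a Kaplan-Meier curve for procedure-related death handles that patient as censored, as if the event could still occur later. The curve then describes a hypothetical population in which nobody dies of anything else. The gap widens with time, because each late procedure death is divided by a risk set that other deaths have already thinned.

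Both ingredients are present here. Deaths from other causes are to be expected in a population that includes incurable disease, and restoration of bowel continuity at 3–6 months falls within the 6-month follow-up. At stake is whether the reported procedure-related risk in each arm can be read as the proportion of randomised patients who die from the treatment strategy, which is how a clinical reader will take it.

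**Working it through.** The article states no mortality assumption or event count for its own analysis, so there is no planned figure to reproduce. The check is how far one minus Kaplan-Meier (1−KM) departs from the true proportion.

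**Inputs from the article.** Follow-up is 6 months, taken as 182 days. There are 120 patients randomised 1:1, so 60 per arm. Background says of emergency operations: "These interventions have a mortality rate of 15–34% and a morbidity rate of 32–64" per cent. The 15% and 34% serve here only to bound total mortality.

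**Assumed, because the article does not give them.** Other causes make up 25–75% of all deaths, spread evenly over 182 days. Early procedure deaths fall evenly on days 1–30 and late ones on days 91–182. The late share of procedure deaths is 0, 20 or 50%.

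**Formulas.** Let *f*(t) be the density of procedure deaths and *S*(t) the proportion still alive. The true risk is the integral of *f*. With other deaths censored, 1−KM = 1 − exp(−∫ *f*/*S* dt). Since *S* ≤ 1, 1−KM is never below the true risk. Over a stretch in which procedure deaths *p* and other deaths *o* both occur evenly, the integral is *p*/(*p*+*o*) × ln(*S* at start / *S* at end).

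**Worked example.** Total mortality is 34%, half of it procedure-related, and half of that late. So early = 8.5%, late = 8.5%, other = 17%, and the true procedure-related risk is 17.0%.

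- Days 1–30: other deaths 0.17 × 30/182 = 0.0280. *S* falls from 1 to 0.8870. Integral = 0.085/0.1130 × ln(1/0.8870) = 0.0902.
- Days 31–90: other deaths only, 0.17 × 60/182 = 0.0560. *S* falls to 0.8309.
- Days 91–182: other deaths 0.17 × 92/182 = 0.0859. *S* falls to 0.6600. Integral = 0.085/0.1709 × ln(0.8309/0.6600) = 0.1145.
- 1−KM = 1 − exp(−0.2047) = 18.5%. The overstatement is 1.5 points.

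**Across the assumed splits** (daily calculation):

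| Total mortality | Late share of procedure deaths | Overstatement, percentage points |
|---|---|---|
| 15% | 0 | 0.03–0.05 |
| 15% | 20% | 0.10–0.13 |
| 15% | 50% | 0.19–0.25 |
| 34% | 0 | 0.18–0.25 |
| 34% | 20% | 0.58–0.78 |
| 34% | 50% | 1.10–1.50 |

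Two settings specified directly fit the same pattern. With 10% early procedure deaths and 5% other deaths, 10.0% is shown as 10.04%. With 10% early, 1% late and 5–15% other deaths, the overstatement is 0.09–0.27 points.

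**Time gradient.** With 10% early and 2% late procedure deaths and other-cause mortality of 5, 10, 20 or 30%, early deaths are inflated by factors of 1.004, 1.008, 1.017 and 1.026. Late deaths are inflated by 1.043, 1.090, 1.199 and 1.333.

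**Scale.** One death in an arm of 60 is 1/60 = 1.7 points. The binomial standard error of a 17% risk in 60 patients is √(0.17 × 0.83/60) = 4.8 points. The overstatement passed one death per arm in only one setting, well outside the quoted range: 10% early, 5% late and 30% other deaths (45% in total) gave 1.94 points.

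**The case against.** **The censoring is inferred.** The article does not say that other deaths will be censored, nor that a risk will be read from the curve, and one sentence in a condensed article may be elaborated elsewhere. This stands as a caution. It does not remove the point, because the article does name a method and applies it to mortality without restriction. Applied as written to a cause-specific outcome, that method implies the censoring.

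**The planned test is sound.** This stands in full. A log-rank test with other deaths censored validly compares cause-specific hazards. Gray's test addresses a different quantity and is no correction of it.

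**The error is too small to matter.** This largely stands. Within the quoted mortality range it is below one death per arm and well below sampling error. The larger figures also need a substantial share of late procedure deaths. That is doubtful: primary anastomosis is allowed, Background notes that many stomas are never closed, and closure is not done where the re-operation risk is judged unacceptable. The sample size rests on quality of life, not mortality.

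**A stronger reading is tempting: that the error tilts the comparison between arms.** A reader might infer that the emergency arm is inflated more because restoration of continuity is described there. For illustration, take a true procedure-related risk of 10% and other-cause mortality of 20% in both arms, with half of the procedure deaths late in one arm and none late in the other. The curves then show about 11.0% against 10.2%. This shows only that unequal error is possible. The article limits restoration to patients with a colostomy, and its section on surgical re-anastomosis is not restricted to the emergency arm. It gives no rates for late procedures or other-cause deaths by arm. Neither the direction nor the size of a between-arm error follows from it.

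**Conclusion.** The point holds as a minor one. The only method named for mortality does not estimate the procedure-related risk that the article lists as an outcome: 1−KM is at or above the actual proportion, increasingly so for late deaths.

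The overstatement is about 0.04 to 0.3 points when procedure deaths are mostly early. It reaches about 1 to 1.5 points only when total mortality is near or above 34% and a large share of procedure deaths is late. All these sizes depend on assumed splits of deaths by cause and time. A reader should not conclude that the mortality comparison as a whole is invalid, or that it favours one arm. The reason to act is that the remedy costs almost nothing.

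**What to change.** Keep Kaplan-Meier curves and the log-rank test for total mortality. For procedure-related mortality, report the Aalen-Johansen cumulative incidence per arm with other-cause death as a competing event, and give the risk difference with its 95% confidence interval at the end of the 6-month follow-up. Keep the log-rank test for this outcome, labelled as a comparison of cause-specific hazards; Gray's test is optional.

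The cost is one sentence in Data analysis and one extra standard estimate, with no new data. Reported procedure-related figures will be slightly lower than 1−KM would give.
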